1. To compare the level of detection of symptoms of prenatal depression, anxiety, and psychosocial risk in e-screening *versus* paper-based screening	Compared to paper-based screening, what is the effect of mental health e-screening in pregnant women on the detection of prenatal depression, anxiety, and psychosocial risk?	Proportion of women scoring above cutoff point of EPDS for depression and anxiety; proportion of women identified as some or high psychosocial risk on ALPHA	EPDS	Compared to the control group, a higher proportion of women in the intervention group will: (1) score 13 or more on the total EPDS (corresponding to probable prenatal depression); (2) score 4 or more on the anxiety subscale of the EPDS (Q3, 4, 5) (corresponding to probable prenatal anxiety); and (3) be identified as having some/moderate or high psychosocial risk on the ALPHA
			ALPHA	
2. To compare the level of disclosure of symptoms of prenatal depression and anxiety, and psychosocial risk in e-screening *versus* paper-based screening	Compared to paper-based screening, what is the effect of mental health e-screening in pregnant women on the disclosure of prenatal depression, anxiety, and psychosocial risk?	Level of disclosure: Mean subscale scores: (1) risk of disclosure; (2) benefits of disclosure	DES	Compared to paper-based screening, e-screening promotes greater disclosure (for example, the mean score risk of disclosure is significantly lower and benefit of disclosure is significantly higher in the e-screening group)
3. To determine factors associated with the acceptability and feasibility of mental health e-screening as well as disclosure	What factors are associated with acceptability and feasibility of mental health e-screening in pregnant women?	Identification of factors that significantly increase odds of acceptability and feasibility of e-screening	Quantitative: (1) Demographic variables (age, gestation, marital status; ethnicity); (2) mental health history; current mental health status; EPDS scores; ALPHA category; (3) DES scores; (4) medical risk; (5) features of the screening instrument/process	Factors that are significantly associated with acceptability and feasibility: mental health history, current mental health status (EPDS, ALPHA), disclosure (DES), medical risk; features of screening instrument
			Qualitative:	
			Semi-structured interviews	
				Factors not associated: demographics

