#### *Data collection procedures*

Procedures related to completion of the psychosocial assessment and baseline questionnaire are described in Procedures. Women will complete the psychosocial assessment on a single occasion. The content and order of individual questions in the e-version of the instruments will be identical to the paper-based version. Women select responses by touching the screen. If a woman does not answer a question, she will be prompted to respond before she can proceed. This is to mimic the usual screening process where the nurse would ask the woman to respond to a missing answer. A ‘SUBMIT’ button at the bottom of the baseline questionnaire will allow women to submit their responses.

The order of material on the tablet will be: (1) Participant Information Letter and Consent; (2) preamble describing the importance of screening and the follow-up with the healthcare provider; (3) ALPHA and EPDS; (4) the CAE, DES, and questions related to acceptability, feasibility, and disclosure; and (5) baseline questionnaire. The content of the baseline questionnaire includes questions that represent factors associated with prenatal mental health or disclosure of mental health concerns, and includes: (1) demographics (age, parity, marital status, education, income, ethnicity, country of birth, and length of time in Canada); (2) obstetrical history (current and past, including use of fertility treatments); (3) mental health history (diagnoses, treatment); (4) level of comfort with technology (for example, laptop, tablet); (5) quality of relationship with perinatal care provider; (6) level of social support, experience of talking with doctor/nurse/midwife about emotional health; and (7) adverse childhood experiences (using ACES questionnaire [48]). With the exception of the ACES (http://acestudy.org/ace_score), questions were derived from the All Our Babies longitudinal birth cohort study (http://www.prehot.org/The%20All%20Our%20Babies%20Study/) and the Maternity Experiences Survey (http://www.phac-aspc.gc.ca/rhs-ssg/survey-eng.php). Participants are required to answer all fields except for income, thus limiting the issue of missing data. Data for the economic evaluation will be collected from program accounts for technology and software costs, and by interviewing clinic staff to estimate clinic operation costs for the two alternatives. We will use a healthcare perspective and all costs will be shown in 2014 values.

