#### *Secondary outcomes*

##### 

**Detection** Differences in proportions of women in the control and intervention group scoring 13 or more on the EPDS, and categorized as some or high-risk on the ALPHA will be estimated using chi-square tests.

##### 

**Disclosure** Comparison of mean scores of the subscales of the DES (risk, benefit of disclosure) will be done using two-tailed independent sample t-tests.

##### 

**Factors associated with acceptability, feasibility, and disclosure** We will use multivariable logistic regression to determine predictors of acceptability, feasibility, and disclosure and report relative risks and 95% CIs. Outcomes will be dichomotized measures of acceptability, feasibility (based on CAE), and disclosure (based on DES) where ‘high’ acceptability, feasibility, and disclosure will include participants whose responses place them above the 75th percentile for the measure. Models will be built using variables that are associated with outcomes at *P* <0.10 on crude analyses, entering demographic variables in a first block, followed by obstetrical factors, mental health history, and the ACES score. Results will be reported as odds ratios and 95% CIs.

##### 

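### Objective 3's regression gives EPDS, ALPHA, DES and screening features no stated place although Table 1 hypothesises them, and a crude P<0.10 screen decides which factors get an adjusted odds ratio

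*Protocol article*

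**What the plan says.** Table 1b of the protocol article, secondary objective 3, lists the factors expected to be associated with acceptability and feasibility: "mental health history, current mental health status (EPDS, ALPHA), disclosure (DES), medical risk; features of screening instrument". The same row adds: "Factors not associated: demographics".

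The analysis for this objective (Analysis, Secondary outcomes, paragraph on factors associated with acceptability, feasibility and disclosure) is multivariable logistic regression. Each outcome is split at the 75th percentile, with feasibility based on the CAE and disclosure on the DES. The selection rule reads "Models will be built using variables that are associated with outcomes at" P "<0.10 on crude analyses". The order of entry is "entering demographic variables in a first block, followed by obstetrical factors, mental health history, and the ACES score".

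Medical risk is listed in Table 1 as a candidate factor ("4) medical risk; (5) features of the screening instrument/process"). The model paragraph does not name it, but the Data collection procedures section describes one baseline domain as "2) obstetrical history (current and past, including use of fertility treatments"), so current obstetrical status may carry it.

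**The concern.** There are two problems.

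First, the hypothesis and the model do not line up. Of the factors hypothesised to matter, only mental health history clearly has a block. Demographics, hypothesised not to matter, enter first. ACES has its own place in the sequence but is not among the Table 1 factors.

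Second, entry depends on a crude P value. A hypothesised factor that misses P<0.10 gets no adjusted estimate, even if confounding masked its crude association. The hypothesis about demographics is poorly served: those that fail the screen disappear without an adjusted interval, and those that pass were chosen because they looked associated. Ordinary 95% CIs are then computed on the data that did the selecting.

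At stake is what objective 3 can conclude about which women find e-screening acceptable and feasible. No between-arm comparison is affected.

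**Working it through.** **1. Table 1 against the model paragraph**

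| Factor | Table 1 hypothesis | Named block |
|---|---|---|
| Mental health history | associated | yes |
| EPDS | associated | none |
| ALPHA | associated | none |
| DES | associated (acceptability, feasibility) | none |
| Medical risk | associated | only if within obstetrical factors |
| Screening features | associated | none |
| Demographics | not associated | yes, first |
| ACES | not listed | yes |

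**2. Number of events**

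The article gives no sample size for these models. Its trial size reproduces: 0.85 × 0.15 × (1.96/0.05)² = 195.9, so 196; 196/0.75 = 261.3, stated as 261 per group, 522 in total. After the planned 25% loss, 522 × 0.75 = 391.5, about 392. Above the 75th percentile means at most 25% events: 0.25 × 392 = 98 and 0.25 × 522 = 130.5.

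**3. What the screen does**

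Assumptions, since the article gives none: one binary predictor, prevalence 30% or 50%, 25% events, kept if crude two-sided P<0.10. The mean kept OR is the exponential of the mean log OR among kept estimates.

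Worked case: N = 522, prevalence 50%, true OR 1.3. Event probabilities of 27.45% and 22.55% average 25% and give OR 1.3.
- SE of log OR = √[1/(261 × 0.2745 × 0.7255) + 1/(261 × 0.2255 × 0.7745)] = 0.203.
- Standardised effect = ln 1.3 / 0.203 = 0.2624/0.203 = 1.29.
- P(kept) = Φ(1.29 − 1.645) + Φ(−1.645 − 1.29) ≈ 0.36.
- Mean kept OR = 1.60.

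Simulation across both sizes and both prevalences:

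| True OR | Kept | Mean kept OR | 95% CI coverage if kept |
|---|---|---|---|
| 1.0 | about 10% | about 1.0 (errors in both directions) | about 50–51% |
| 1.3 | 28–36% | 1.60–1.73 | 90–93% |
| 1.5 | 50–64% | 1.69–1.83 | 95–96% |
| 2.0 | 88–96% | 2.04–2.12 | 97–98% |
| 2.5 | 98% or more | 2.50–2.53 | 95–97% |

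A rarer factor fares worse: at 15% prevalence, a true OR of 1.5 is kept 39% (N = 392) to 46% (N = 522) of the time, with mean kept OR 2.02 to 1.88. Without the screen, the geometric mean estimate for a true OR of 1.5 is 1.50.

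**4. What leaving EPDS out can do**

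Assume 30% of women have a mental health history, EPDS is positive in 30% of them and about 10% of the others, EPDS has OR 1.5–3, and mental health history has no effect of its own. With EPDS omitted, the mental health history OR becomes 1.09–1.29 instead of 1.0. The one hypothesised factor that clearly has a block can therefore pick up the effect of one that does not.

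**The case against.** The strongest reply is that this is an exploratory secondary objective, that the screening rule is disclosed, and that a condensed article may give an order of entry without the full candidate list. Several parts of it stand.

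- A reader might infer that the model cannot test the hypothesis at all. The text does not support that. Table 1 says associated, not independently associated, and the crude analyses address crude association. Mental health history and demographics are in named blocks, and the block list is not declared exhaustive.
- A reader might infer that medical risk is omitted. It is unclear, not omitted, because obstetrical history covers the current pregnancy.
- DES defines the disclosure outcome, so its absence from that model is correct. It matters only for acceptability and feasibility.
- A reader might infer that the reported intervals are generally invalid. They are not. Coverage among kept factors is 90–93% at OR 1.3 and about nominal or above from OR 1.5. The 50% figure belongs to exactly null factors that pass. Unconditionally, 0.10 × 0.50 = 0.05 of null factors pass and reach P<0.05, so in this crude-test calculation the screen adds no false positives.
- The sizes are for crude estimates, conditional on selection; the protocol would report multivariable ones.

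What does not stand is the idea that nothing needs changing. The current text gives a definite sequence that differs from its own hypothesis, and a definite rule that withholds adjusted estimates from hypothesised factors.

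**Conclusion.** The mismatch is real and the selection rule is poorly chosen for this objective. As written, EPDS, ALPHA and screening features have no stated place in the adjusted models, nor does DES where it is hypothesised. Medical risk has only an implied place, and no hypothesised factor is assured an adjusted odds ratio.

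The screen matters most for weak factors: a true OR of 1.3 would be dropped roughly two times in three and, when kept, would average about 1.6–1.75. It matters little at OR 2 and hardly at all at 2.5. These sizes rest on assumed predictor prevalences and true odds ratios, and on 98 to 130 events as a ceiling. The mismatch between Table 1 and the model paragraph rests on no assumption. Because the objective is secondary and only wording is needed, this should be changed before analysis, but it does not threaten the trial's main comparison.

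**What to change.** Replace the crude P<0.10 screen with one prespecified model per outcome, containing the Table 1 factors plus demographics and arm:

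- Give EPDS, ALPHA, medical risk and screening features named terms, and say which variables represent the screening features.
- Use DES as a predictor only in the acceptability and feasibility models.
- Enter medical risk or setting, not both. High- and low-risk women are recruited largely through different site types, so the two terms would be nearly collinear.
- Say whether ACES is a hypothesised factor, and align Table 1 with the model.
- Report every adjusted odds ratio with its CI, whatever its P value.

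At an assumed 10 events per parameter, 98 to 130 events support about 10 to 13 parameters. The full list may exceed that once ALPHA categories, two DES subscales and multi-level demographics are counted. If so, reduce terms by subject matter or use penalised regression, not crude P values.

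The cost is analysis-plan wording and somewhat wider intervals for some terms. EPDS, ALPHA and DES are already collected.

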4. To compare the psychometric properties (sensitivity, specificity, cutoff points) of paper-based ALPHA and EPDS *versus* the e-version administered to medically low- and high-risk pregnant women	Are the psychometric properties (for example, sensitivity, specificity, cutoff points) similar or better in the ALPHA and EPDS e-version compared to the paper-version when administered to pregnant women?	Psychometric properties: sensitivity, specificity of ALPHA and EPDS in paper-based and e-versions	ALPHA, EPDS, MINI	The psychometric properties of e-version of ALPHA and EPDS are similar or better compared to paper-based version
5. To compare the cost-effectiveness e-screening compared to paper-based screening	Is e-screening as a component of routine prenatal care cost effective when compared to paper-based screening?	Cost-effectiveness: actual costs	The expected incremental cost effectiveness of e-screening is cost effective at values of health considered acceptable in the Canadian healthcare system	E-screening will be cost effective

ALPHA: Antenatal Psychosocial Health Assessment; CAE: CASI Assessment Evaluation; DES: Disclosure Expectations Scale; EPDS: Edinburgh Postnatal Depression Scale; MINI: Mini International Neuropsychiatric Interview.

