## Methods/Design

### Study design

The study is a parallel-group, randomized, controlled superiority trial (RCT) with a qualitative descriptive component (Figure 1). This design is well-suited for answering questions of effectiveness, acceptability, and feasibility [47]. In this trial, physicians and all research assistants conducting diagnostic interviews are blinded. We adhered to CONSORT guidelines in the design of the trial [45,46] and the SPIRIT guidelines [48,49] in reporting its details in this protocol. Approval for this study was granted by the Human Research Ethics Board at the University of Alberta.

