#### *Recruitment procedures, consent, randomization, and allocation procedures*

Recruitment procedures are similar across sites. Trained staff at the recruitment sites will use a standardized script to determine each eligible (see Eligibility criteria) woman’s interest in study participation. Women will be referred to an onsite research assistant who will provide the tablet. Women will complete the consent electronically on the tablet and receive the automatically generated copy via email. The research assistant will be available to answer questions about study participation and tablet logistics. A simple, computer-generated randomization process designed by the Women’s and Children’s Health Research Institute (WCHRI) at the University of Alberta allocates women (1:1 ratio) automatically to the control or intervention group, and they will receive a ‘pop-up’ message informing them that they will complete questions about emotional health on paper (control group) or tablet (intervention group). Computerized randomization preserves allocation concealment and reduces the possibility of selection bias since the research assistant is kept unaware of the group assignments until after the participants are allocated to groups.

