#### *Procedures*

##### 

**Maternity clinics** At the maternity clinic recruitment sites, each eligible woman will complete the ALPHA and EPDS while they wait for their prenatal appointment - either via computer tablet or paper. After randomization to the control group, a message appears on the tablet, directing women to complete the ALPHA and EPDS on paper. An automatic ‘skip’ procedure ensures that the electronic versions of the ALPHA and EPDS are bypassed for women in the control group. Following completion of the paper-based psychosocial assessment, women will proceed to complete the baseline questionnaire on the tablet. Women in the intervention group will be directed to answer questions about emotional health (ALPHA and EPDS) and the baseline questionnaire on the tablet. All questions require responses, and thus women cannot proceed past questions with missing answers until completed. In keeping with the current clinic processes of including the assessment in the medical record, the electronic copy will be printed following completion. As is usual care in the maternity clinics, a Registered Nurse will review the assessment, judge whether women are at low, some, or high risk, discuss women’s psychosocial assessment responses with them, and provide follow-up referrals for those with some or high psychosocial risk with a mental health nurse affiliated with the clinic.

##### 

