**Psychometric properties** Psychometric properties of internal consistency (Cronbach’s alpha; item-total correlation) will be calculated for the EPDS by modality. Predictive validity measures of sensitivity, specificity, positive predictive value, and negative predictive value will be calculated using clinical interview diagnosis as the reference. Comparisons of the psychometrics between the two modalities will be made by correlational analysis using Cohen’s guidelines [59]. In terms of further tool development of the ALPHA, we will develop an integer score-based prediction rule for the prevalence of anxiety and depression, according to MINI diagnosis. This method was previously used to develop a prenatal screening tool for postpartum distress by two members of the research team (SM, DK) [60]. We will develop a best fit multiple regression model predicting depression and/or anxiety as per clinical interview diagnosis, candidate variables for which will be drawn from the ALPHA. A regression coefficient-based scoring algorithm [60] will be applied to the final regression model in order to develop a single screening score. Receiver operating characteristic (ROC) analysis will then be used to determine an optimal cutoff for the screening score. Finally, we will perform a ROC analysis for each modality (e-version *versus* paper-based) and compare indices of sensitivity, specificity, positive and negative predictive values using Cohen’s guidelines [60]. All analyses will be conducted in the total sample, with subgroup analyses conducted by medical risk to determine whether the scoring is robust across risk subgroups.

##### 

**Cost-effectiveness** For the economic analysis, we will estimate the incremental costs-effectiveness (ICER) for the e-screening alternative compared to the paper-based alternative. The e-screening costs include investment costs to technology (programs, tablets, data storage) and the operating costs at the clinic that may differ somewhat from the conventional group administrative and analytical cost. Cost-effectiveness is determined by incremental cost to identify a woman with increased risk of prenatal and postpartum depression and anxiety. Because we are not going to follow up the screened women, the costs and outcomes after the screening are not included in this initial economic analysis.

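### Secondary objective 4: correlation and Cohen's effect-size labels cannot compare paper and tablet accuracy between independent arms, and the new ALPHA score is evaluated in the women it is derived from

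*Protocol article*

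**What the plan says.** The design is parallel-group: "The study is a parallel-group, randomized, controlled superiority trial (RCT) with a qualitative descriptive component". The randomization system "allocates women (1:1 ratio) automatically to the control or intervention group". Data collection procedures adds: "Women will complete the psychosocial assessment on a single occasion". At the maternity clinics the assessment is done "either via computer tablet or paper", and a programmed skip "ensures that the electronic versions of the ALPHA and EPDS are bypassed for women in the control group". The antenatal unit follows the same scheme. The article describes no crossover, repeat administration or paired substudy.

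Table 1b gives the hypothesis for objective 4: "The psychometric properties of e-version of ALPHA and EPDS are similar or better compared to paper-based version". The properties it names are sensitivity, specificity and cutoff points; the list of secondary objectives adds predictive values.

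Under Analysis, Secondary outcomes, the Psychometric properties paragraph plans Cronbach's alpha and item-total correlations for the EPDS by modality, and sensitivity, specificity and predictive values against the clinical interview. It then says how the modalities will be compared: "Comparisons of the psychometrics between the two modalities will be made by correlational analysis", with Cohen's guidelines as the yardstick.

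For the ALPHA, which has no existing score or cutoff, the same paragraph sets out a sequence: a best-fitting regression on the trial's own MINI diagnoses, integer points from its coefficients, and then "Receiver operating characteristic (ROC) analysis will then be used to determine an optimal cutoff for the screening score". ROC analysis by modality follows, with the indices again compared by Cohen's guidelines. The analyses use the total sample, with subgroups by medical risk.

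**The concern.** Objective 4 asks whether one version of an instrument is at least as accurate as the other. Sensitivity, specificity and predictive values are single numbers per arm, so in two independent groups the question is how far those numbers differ and how precisely that is known. A correlation does not answer this, and an effect-size label gives neither a test nor an interval. A difference labelled small could be read as similarity even if the data were too few to rule out a substantial loss of sensitivity.

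For the ALPHA, a model and a cutoff chosen to fit a set of women will look better in those women than in new ones. The subgroups by medical risk contain the same women, so they are not a validation. Secondary outcomes gives support for clinical decision-making as the reason for wanting an algorithm, so an overstated accuracy would matter.

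**Working it through.** **1. The plan's own figure.** Table 2: n = 0.85 × 0.15 × (1.96/0.05)² = 195.9, so 196; 196/(1 − 0.25) = 261.3, stated as 261. This reproduces. The calculation concerns acceptability and disclosure proportions, not objective 4, but it supplies the arm sizes used below: 261 randomized and 196 after attrition.

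**2. Paired data.** One administration per woman in one modality leaves 0 women with both a paper and a tablet score.

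**3. What correlation could do.** Item-total correlations, or the correlation of score with MINI diagnosis, can be computed within each arm and contrasted as independent coefficients. By Fisher's z, the Cohen's q detectable with 80% power is (1.96 + 0.84) × √(2/(n − 3)) = 0.29 with 196 per arm and 0.25 with 261. The article does not describe this contrast, and it would not compare sensitivity, specificity or predictive values.

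**4. Precision of a between-arm difference.** Inputs: EPDS sensitivity 85% and specificity 77% (The intervention), assumed equal in both arms; prevalence 13% to 29% (Introduction), assumed to apply to MINI diagnoses. Half-width = 1.96 × √(2p(1 − p)/m), where m is cases per arm for sensitivity and non-cases for specificity.

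| Women per arm | Prevalence | Cases per arm | Half-width, sensitivity difference | Drop detectable at 80% power | Half-width, specificity difference |
|---|---|---|---|---|---|
| 196 | 13% | 25 | 0.198 | 0.365 | 0.089 |
| 196 | 29% | 57 | 0.131 | 0.230 | 0.099 |
| 261 | 13% | 34 | 0.170 | 0.308 | 0.077 |
| 261 | 29% | 76 | 0.114 | 0.195 | 0.086 |

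First row: 1.96 × √(2 × 0.1275/25) = 0.198.

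The recruitment mix points to the upper part of the range. The article gives 50 clinic and 45 antenatal-unit women per month, and more than three times the prevalence in high-risk women. Assuming 13% in low-risk and 39% in high-risk women, the mix is (50 × 0.13 + 45 × 0.39)/95 = 25.3%. That gives about 50 cases among 196 women (half-width 0.14) or 66 among 261 (0.12).

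**5. ALPHA score.** The article gives neither the number of candidate items nor their strength, so these are assumed. Two simulations drew 15 or 35 yes/no items, screened them at P < 0.10, eliminated backward at P < 0.05, assigned integer points and chose the cutoff by the Youden index. Each score was then tested in new women.

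- With 392 or 522 women and about 60 to 80 cases: AUC 0.70 to 0.72 in the same women and 0.64 to 0.66 in new women; Youden index 0.31 to 0.35 and 0.20 to 0.24.
- With 392 or 542 women, nominal prevalence 15% or 25%, and five true predictors with odds ratio about 1.8: AUC 0.67 to 0.69 in the same women and 0.60 to 0.64 in new women; Youden index too high by 0.06 to 0.16.
- A third run, with the same selection steps, five true items with odds ratio 1.8 and 25% endorsement: AUC too high by 0.056 to 0.111 at 15% prevalence and by 0.029 to 0.075 at 29%.

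The direction is the same in all three. The AUC excess runs from about 0.03 to 0.11 and shrinks as cases increase.

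**The case against.** The strongest defence is that the article never says paper scores will be correlated with tablet scores. It speaks of comparing psychometrics, and those it has just listed include item-total correlations, which need no pairing. Cohen's guidelines also cover independent proportions, and the cited source cannot be consulted here. This stands in part. A reader might infer that no correlation can be computed, or that objective 4 has no analysis at all. Neither follows: within-arm correlations exist, and indices and ROC analyses by modality are planned, which is an independent-arm structure. What does not stand is the stated means of comparing those indices.

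On the ALPHA, the defence is that internal validation may be in the unseen analysis plan, that using the total sample does not exclude a bootstrap, and that the work is presented as tool development. All of this is fair. The absence of the word bootstrap is not the point; the stated sequence of derivation, cutoff and evaluation in one sample is. A reader might also infer that an unvalidated score will be published as accurate and put into use. The article gives a rationale for having an algorithm, not a plan to deploy this one. Likewise, multiple regression for a binary diagnosis need not mean a linear model; it may be loose wording, since logistic regression is named for the other binary outcomes.

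Finally, the case counts may be too low: high-risk women are enrolled, and on the antenatal unit the MINI is done at recruitment, so 25% attrition is doubtful there. That would narrow the intervals, but the mismatch of method does not depend on prevalence.

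**Conclusion.** The point holds in a limited form. The stated comparison method does not suit two independent arms for the properties that objective 4 names, and cannot support a claim that the e-version is at least as good. With a suitable method, the sensitivity difference would carry a half-width of about 11 to 20 points, assuming 13% to 29% prevalence, 85% sensitivity in both arms and 196 to 261 women per arm; more cases would narrow it. Even with identical observed sensitivities, a margin tighter than the half-width could not be met, so this part of the objective is mainly estimation.

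The ALPHA score's apparent accuracy will be optimistic, by roughly 0.03 to 0.11 in AUC under assumed items, predictor strengths and prevalence. This bears on the score's absolute accuracy. Both arms contribute to the derivation, so it need not bias the paper-tablet contrast to the same degree.

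The primary outcome, sample size and randomization are untouched. This is a should-fix on one of five secondary objectives.

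**What to change.** Replace the correlational comparison with between-arm differences for independent samples, each with a 95% CI: for example Newcombe intervals for sensitivity and specificity at the EPDS cutoffs, an unpaired DeLong comparison for AUC, and Feldt's test for Cronbach's alpha. Claim similarity only if the interval lies within a margin fixed and justified before the data are seen; otherwise report the comparison as estimation. Within-arm correlations may stay as description.

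For the ALPHA score, name logistic regression, bootstrap the whole derivation (item selection, integer points and cutoff), and report optimism-corrected AUC, sensitivity and specificity overall and by modality.

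The cost is a change of analysis wording and a few hours of programming, with no change to design, recruitment or data collection. The reported ALPHA accuracy will be less favourable, and the intervals will show how little the trial can say about small differences in sensitivity; the change does not cure that imprecision.
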